## Methods

CANCER COG is a multicenter prospective longitudinal study with the constitution and the follow-up of 4 cohorts, including:

Three cohorts of patients candidate for a brain irradiation following the diagnosis of benign meningioma or atypical meningioma:
Cohort “IMRT”: Patients receiving normo-fractionated intensity-modulated brain irradiation with or without stereotactic positioning (IMRT, VMAT, Tomotherapy…).Cohort “SRT”: Patients receiving hypo-fractionated stereotactic brain irradiation.Cohort “PRT”: Patients receiving normo-fractionated proton therapy brain irradiation.
In addition, a control group with participants free of brain disease will be constituted:
Control cohort: Participants without any meningioma or neurological comorbidities.

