### Trial schedule

CANCER COG is a multicenter prospective longitudinal study with the constitution and the follow-up of 4 cohorts:

Cohort “IMRT”: Patients receiving normo-fractionated intensity-modulated brain irradiation with or without stereotactic positioning (IMRT, VMAT, Tomotherapy…).Cohort “SRT”: Patients receiving hypo-fractionated stereotactic brain irradiation.Cohort “PRT”: Patients receiving normo-fractionated proton therapy brain irradiation.Control cohort: Participants without any meningioma or neurological comorbidities.

The overall duration of the project is estimated to 15 years, including 5 years of inclusion and around 10 years of participation.

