### Statistical design overview

The primary endpoint is the proportion of patients with an impairment in cognitive parameters 10 years after irradiation of skull base benign meningioma, or atypical meningioma.

As there are no available data in the literature concerning the prevalence of long-term cognitive disorders after radiotherapy treatment of skull base benign meningioma, or atypical meningioma, we assume that approximately 50% of patients will present an impairment of their cognitive functions 10 years after the end of irradiation. Using a 95% confidence interval with a width of 0.2 for a small sample size, a total of 93 patients is required.

In order to document the impact of brain irradiation on cognitive performances for each of the 3 radiotherapy modalities usually used in this indication, 31 patients are required in each of the 3 cohorts (IMRT, SRT, PRT).

In addition, a control group with 31 assessable participants free of brain disease will be constituted.

In order to anticipate 15% of subjects possibly non assessable, 36 subjects per each of the 4 cohorts will be enrolled, for a total of 108 patients and 36 participants free of brain disease.

Categorical variables will be summarized using numbers and proportions. Quantitative variables will be summarized using quartiles and range (mean and standard deviation for Gaussian-like variables). The pattern of missing data will be described.

Briefly, all outcomes will be analyzed based on intention-to-treat principle. For each cohort, the Intention to Treat (ITT) population is defined as all patients included in this radiation arm, regardless of whether eligibility criteria are met and whether or not radiation therapy is used.

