#### Secondary objectives

At the patient level: no comparison between arm is planned in analyses.

The Progression-Free Survival (PFS) time is defined as the time elapsed from treatment start to progression disease or death from any cause. Data of patients who did not experience event are censored at the last assessment date. PFS will be estimated by the Kaplan-Meier method. The evolution of health-related quality-of–life after irradiation will be described by mean and standard error, and compared across time by the Student t test for paired data.

With regard to radiotherapy parameters: in each cohort, the correlation between dosimetric data (quantitative data) and the occurrence of cognitive deterioration will be assessed by the non-parametric Wilcoxon Mann Whitney test.

With regard to brain MRI parameters: In each cohort, association between alterations or modifications of grey and white matters after irradiation on brain MRI and cognitive deterioration will be assessed by the exact Fisher test.

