#### Patient withdrawal

The participation to the study will be interrupted at any time under the following circumstances:

Patient request (data already collected during the study will be stored and used unless the patient expresses his/her opposition, withdrawal of consent for further treatment).Patient may stop to participate to the study at any time, on his/her request, without any requirement to justify the study withdrawal. The withdrawal may be given orally or in writing. However, the investigator is responsible to take note of reason for study withdrawal, without question the patient’s wish, and has to document it, as well as the date of withdrawal.Concomitant disease or other reason requiring the discontinuation of study participation.Investigator’s request (with detailed documentation of reasoning).Non-compliance of patient.patient lost to follow-up.Trial termination by the sponsor.Death.

Any patient who prematurely withdraws from the study treatment only will continue to be followed, unless she withdraws from the study.

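### The intention-to-treat set keeps never-irradiated patients in a proportion defined after irradiation, where nothing is randomised and no between-arm comparison is planned

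*Protocol article*

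**What the plan says.** All statements are in the protocol article.

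- **Analysis set (Statistical design overview).** "Briefly, all outcomes will be analyzed based on intention-to-treat principle". Each cohort's set is then everyone included in it, "regardless of whether eligibility criteria are met and whether or not radiation therapy is used".
- **Endpoint (same section).** "The primary endpoint is the proportion of patients with an impairment in cognitive parameters 10 years after irradiation of skull base benign meningioma"; the definition covers the atypical form as well. Primary objective (analysis) estimates this proportion with a 95% confidence interval in each cohort.
- **Cohorts (Methods, Trial schedule).** They are defined by treatment received, for example "Patients receiving normo-fractionated proton therapy brain irradiation" and "Patients receiving normo-fractionated intensity-modulated brain irradiation". The lead-in under Methods also calls the patients candidates for brain irradiation.
- **Clock.** Follow up after irradiation dates every visit from the end of radiotherapy. Secondary objectives (analysis) defines progression-free survival (PFS) as the "time elapsed from treatment start to progression disease or death from any cause".
- **Sequence.** Under Irradiation, radiotherapy starts within six weeks after inclusion. Under Patient withdrawal, someone who leaves only the study treatment is still followed.
- **Allocation and comparison.** The radiation oncologist chooses the modality (Study procedures), and the secondary analyses at patient level exclude comparisons between arms.

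**The concern.** In a randomised comparison, ITT earns its place by keeping the groups as they were allocated. Here nobody is allocated at random and each cohort is described on its own, so the principle has nothing to protect. What it does is bring into a radiation-toxicity estimate patients who may have had no radiation.

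At stake is the meaning of the primary proportion. A reader will take it as the risk after treatment with a given modality. Unexposed patients in numerator and denominator pull it towards whatever their own rate is. If that rate is lower, radiotherapy looks safer than it is, which is the unfavourable direction for a study of late harm.

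**Working it through.** **1. Can the set be applied as written?** Take a patient who is included and never irradiated. This is possible because inclusion comes first.

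| Quantity | What it needs | Does this patient have it? |
|---|---|---|
| Membership of the ITT set | Inclusion in the cohort | Yes |
| Ten-year primary assessment | End-of-radiotherapy date | No |
| PFS | Treatment start date | No |
| Dosimetric analysis | Delivered dose | No |

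Either the patient is left out for want of a date, and the ITT rule is not followed, or a substitute date is used, and an unexposed patient enters the estimate. The text does not say which.

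**2. The plan's own figures.** Inputs from Statistical design overview: expected proportion 0.50, 95% interval of full width 0.20, 93 patients, 31 per cohort, 36 enrolled to allow for 15% non-assessable.

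- The Wilson interval at p = 0.5 has width 0.2002 for n = 92 and 0.1992 for n = 93, so 93 is reproduced exactly.
- 31 × 1.15 = 35.65, rounded up to 36, reproduces the enrolment figure. Dividing instead, 31 / 0.85 = 36.47, gives 37, a difference of one patient that does not matter here.
- At n = 31, the level at which the proportion is reported, the Wilson interval at p = 0.5 runs from 0.334 to 0.666, a width of 0.332.

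**3. Possible size of the effect.** Let f be the share of the analysed cohort never irradiated but assessed at ten years, and p0 their deterioration rate. With the plan's 0.50 in irradiated patients:

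reported proportion = (1 − f) × 0.50 + f × p0

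Both f and p0 are assumptions; the documents give neither.

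| f | p0 = 0 | p0 = 0.05 | p0 = 0.30 | p0 = 0.50 |
|---|---|---|---|---|
| 1 of 36 (2.8%) | 48.6% | 48.75% | 49.4% | 50% |
| 5% | 47.5% | 47.75% | 49.0% | 50% |
| 10% | 45.0% | 45.5% | 48.0% | 50% |
| 15% | 42.5% | 43.25% | 47.0% | 50% |

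One patient in 36 lowers the estimate by 0.6 points (p0 = 0.30) to 1.4 points (p0 = 0). With p0 = 0.05, the shift is 50 − 47.75 = 2.25 points at 5% and 50 − 45.5 = 4.5 points at 10%. If p0 equals 0.50 there is no shift.

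**The case against.** The case for leaving the text alone is that few patients should be affected. Inclusion requires an irradiation indication confirmed at a multidisciplinary meeting, and treatment follows within six weeks. One unirradiated patient per cohort moves the result by under 1.5 points against an interval about 33 points wide. The cohort lead-in speaks of candidates, which suits a set based on inclusion, and the paragraph presents itself as a summary. All of this stands as a limit on size, and it means the cohort descriptions are loosely worded rather than flatly opposed to the ITT definition. It does not remove the mismatch, because the rule is stated explicitly, covers all outcomes and names non-irradiation as no bar to inclusion.

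Four stronger readings are tempting and are not supported:

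- **That the proportion is diluted.** This needs unirradiated patients to exist, to be tested at ten years and to deteriorate less. None of this is documented. Ineligible patients who were irradiated could move the estimate either way.
- **That the denominator is contradictory, because the sample size counts assessable patients and the analysis counts everyone included.** Enrolling 36 to obtain 31 is an ordinary attrition allowance and is compatible with an ITT set. How the untested are counted does matter: 16 impaired of 31 is 51.6%, while over 36 it is 16/36 = 44.4% or 21/36 = 58.3%, depending on how the other five count. But that range runs in both directions, would arise with any analysis set, and its rule may sit in the analysis plan.
- **That patients who decline cognitively will be the missing ones, because "Non-compliance of patient" ends participation.** This is conjecture. The same section keeps treatment-only withdrawals in follow-up.
- **That patients will be counted under the wrong modality after a switch.** The article does not mention switching.

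**Conclusion.** The point holds as a mismatch between the stated analysis set and the quantity it is meant to estimate. It rests on the article's own wording: a set that admits never-irradiated patients, an endpoint and visit schedule timed from irradiation, and a non-randomised, descriptive design in which ITT offers no compensating advantage.

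The possible bias is towards a lower toxicity rate, on the condition that unirradiated patients are assessed and deteriorate less. Its size cannot be derived from the documents. Under the assumptions tabulated it is 0.6 to 1.4 points for one patient in 36 and 2.25 to 4.5 points at 5 to 10% with a 5% background rate, in each case well inside the per-cohort uncertainty. This is a cheap improvement to a stated rule, not a flaw that undermines the study.

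**What to change.** In Statistical design overview, define the primary analysis set for each cohort as included patients who started irradiation, grouped by the modality received. List never-irradiated patients separately, with their number per cohort, and report the present ITT set as a sensitivity analysis.

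The cost is one changed definition and one additional analysis, with no new patients, visits or sample-size calculation. The downside is that the primary estimate no longer carries the ITT label, although the ITT result is still reported beside it. Inclusions began in 2023, so no ten-year result can exist before 2033 (2023 + 10), and the change can be made before any primary outcome is seen.

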#### Primary objective

The proportion of patients with an impairment in cognitive parameters 10 years after irradiation of skull base grade I-II meningioma will be estimated with a 95% confidence interval in each cohort.

#### Secondary objectives

At the patient level: no comparison between arm is planned in analyses.

The Progression-Free Survival (PFS) time is defined as the time elapsed from treatment start to progression disease or death from any cause. Data of patients who did not experience event are censored at the last assessment date. PFS will be estimated by the Kaplan-Meier method. The evolution of health-related quality-of–life after irradiation will be described by mean and standard error, and compared across time by the Student t test for paired data.

With regard to radiotherapy parameters: in each cohort, the correlation between dosimetric data (quantitative data) and the occurrence of cognitive deterioration will be assessed by the non-parametric Wilcoxon Mann Whitney test.

With regard to brain MRI parameters: In each cohort, association between alterations or modifications of grey and white matters after irradiation on brain MRI and cognitive deterioration will be assessed by the exact Fisher test.

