**Methods:**

CANCER COG is one of the first multicentric study in the world to prospectively assess the cognitive performances of patients following different modalities of cerebral radiotherapy (stereotactic radiotherapy, proton therapy, intensity modulated radiotherapy) for the treatment of grade I-II skull base meningioma, up to at least 10 years after the end of radiotherapy. This longitudinal study includes the follow-up of 3 cohorts, including: patients treated with PRT, IMRT, and SRT. An additionally control group will be formed. The primary objective is to report long-term cognitive deterioration in each cohort until 10 years after the end of irradiation. The rate of clinical symptomatology improvement over time after irradiation, the evolution of health-related quality-of-life, anxiety/depression, fatigue, over time after irradiation, the tumoral local control after irradiation, the progression-free survival (PFS), the professional reintegration for working-age patients will also be assessed. CANCER COG aims to help clinicians to choose the best irradiation techniques with the best benefit/risk ratio. Inclusions started on september 2023.

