## Hypothesis and expected clinical outcomes

Following these observations, we herein propose the first study in France to prospectively assess the cognitive performances of patients following different modalities of cerebral radiotherapy (stereotactic radiotherapy, proton therapy, intensity modulated radiotherapy) for the treatment of low grade skull base meningioma, up to at least 10 years after the end of radiotherapy. This project is elaborated with the expertise of the National Cancer and Cognition Platform (http://www.canceretcognition.fr/), as well as of the National Clinical research Platform for Quality of Life in Oncology, both labelled by the French League against Cancer (LNC).

For the purpose of this research, we will constitute several cohorts of patients, treated either by intensity-modulated radiotherapy, stereotactic radiotherapy or proton-therapy. This will allow better understanding the cognitive and anatomical damages caused by new radiotherapy techniques and better understanding how ionising radiation (X-rays or protons) acts in the long term on brain tissue. Longitudinal follow-up will be multimodal, based on yearly multi-parametric brain MRI to assess morphological changes [9–11], in relation with dosimetric data as well as neuropsychological performances, health-related quality of life, anxiety and depression disorders, memory tasks, and socio-professional reintegration. This will notably make it possible to evaluate the relationship between dosimetric data, age at the time of treatment, region of the brain irradiated, type of radiation used, dose per fraction, neurocognitive and neuro-anatomical consequences. A Normal Tissue Control Probability (NTCP) model will be also developed. Overall, the results of this study should contribute to the improvement of treatment techniques, in particular by preserving as much as possible the significant cerebral zones (hippocampi, frontal lobe, sub-ventricular zones, etc.), and to the management of patients by proposing appropriate support measures. In the proton-therapy cohort, evaluations will make it possible to establish more precisely the place that this new irradiation strategy should occupy in the management of low grade meningioma. Importantly, we have planned to constitute a last cohort, with subjects free of any neurological disease, to make it easier the interpretation of cognitive performances over time among patients in the three brain radiation cohorts.

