### Study procedures

Eligible patients will be identified by the local multidisciplinary staff among patients with an indication of brain irradiation following the diagnosis of benign meningioma or atypical meningioma. The decision of radiotherapy should be made by the local multidisciplinary committee of each investigator center. Once checked all eligibility criteria, the radiation oncologist will propose the study to patients. Patients will be given study information (explanation on the study, reading and giving of the information notice). Patients will have a reflection period of the duration of their choice.

The specific exams/procedure requested in the study before inclusion (baseline visit) will be performed after consent signature and before inclusion. Inclusion will be thus performed.

The choice of the irradiation modality is at the discretion of the radiation oncologist: hypo-fractionated stereotactic radiotherapy (SRT), normo-fractionated intensity-modulated radiotherapy (IMRT), or proton-therapy (PRT) according to each center routine.

For enrolled patients, within 6 weeks before inititation of brain irradiation, the following evaluations will be performed in the investigator center. Procedures are summed up in Table 2.

**Table 2 Tab2:** Study procedures

	Screening before inclusion	Baseline assessment (within 6 weeks before radiotherapy start)	During radiotherapy period (7 weeks) for 3 cohorts: - Cohort IMRT - Cohort SRT - Cohort PRT	End of radiotherapy	AFTER THE END of radiotherapy	
					6 and 12 months	Yearly up to 10 years
Study explanation and signed informed consent before any study procedures	✓					

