## Discussion

Given the excellent prognosis of skull base meningioma, every effort should be done to avoid radiation induced long-term toxicities, particularly, neuro cognitive impairment. Modern technical of irradiation are widely used in this indication, and lead to a better protection of healthy tissue.

However the clinical proof level of these technical (IMRT, PRT, SRT), concerning any cognitive benefit, remains poor. Randomized trials are difficult to set up due to issues such as access to proton-therapy.facilities. CANCER COG results will be crucial to help radiation oncologists to choose the most appropriate irradiation technical.

First inclusions started on August 2023. Final results are expected between 2030 and 2035.

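### The plan analyses each cohort separately and compares none, so it cannot support its claims about radiation type, dose per fraction and choice of technique

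*Protocol article*

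**What the plan says.** On analysis, the protocol article's Primary objective section (under Statistical design overview) gives one proportion with a 95% confidence interval per cohort. The Secondary objectives section that follows states, for the patient level, that "no comparison between arm is planned in analyses". For radiotherapy parameters it specifies that "in each cohort, the correlation between dosimetric data (quantitative data) and the occurrence of cognitive deterioration will be assessed" by a Wilcoxon-Mann-Whitney test. The association of MRI changes with deterioration is likewise tested cohort by cohort, with Fisher's exact test.

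On purpose, the Abstract (Methods) says: "CANCER COG aims to help clinicians to choose the best irradiation techniques with the best benefit/risk ratio". The Discussion says: "CANCER COG results will be crucial to help radiation oncologists to choose the most appropriate irradiation technical". The section Hypothesis and expected clinical outcomes says the follow-up will allow evaluation of the relationship between dosimetric data and a list that includes "age at the time of treatment, region of the brain irradiated, type of radiation used, dose per fraction, neurocognitive and neuro-anatomical consequences".

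On allocation, Study procedures states: "The choice of the irradiation modality is at the discretion of the radiation oncologist". The Irradiation section excludes SRT for grade II tumours, and the Abstract (Background) describes SRT as the technique for small tumours.

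**The concern.** Choosing between techniques is a comparison, and so is estimating the effect of protons against photons or of large against small fractions. The article announces these as products of the study, while its analysis sections work inside one cohort at a time. The likely result is that three crude proportions are set side by side and read as evidence on modality, although the cohorts differ by construction in grade and, by the article's own account, in tumour size.

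A second consequence concerns a question the design can address. Dose to brain structures can vary between patients in the same cohort, so a dose-cognition association can be studied. Splitting it into three tests of 31 patients leaves each with little power, and no overall test is specified.

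**Working it through.** **1. Where each factor varies** (protocol article, Methods and Irradiation)

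| Cohort | Radiation | Dose per fraction | Grades treated |
|---|---|---|---|
| IMRT | photons | 1.8–2 Gy | I and II |
| SRT | photons | 5 Gy | I only |
| PRT | protons | 1.8–2 Gy | I and II |

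- Photon against proton: no variation inside any row, so a within-cohort test carries no information on it at any sample size.
- Dose per fraction: constant in SRT. The 1.8 to 2 Gy range in the other two cohorts cannot inform a contrast with 5 Gy, which exists only between cohorts.
- A model fitted to all patients does not separate these factors from cohort either. Radiation type and the 5 Gy contrast are functions of cohort membership, which follows clinician choice, grade and tumour size.

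**2. The plan's own sample size** (Statistical design overview: 50% rate, 95% interval of width 0.2, 93 patients, 31 per cohort)

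- Wald: 1.96² × 0.25 / 0.10² = 96.04, giving 97.
- Wilson: 96.04 − 1.96² = 96.04 − 3.84 = 92.20, giving 93. The stated figure is reproduced.
- The 0.2 width belongs to the pooled 93. At 31 the Wilson half-width is 0.166, a width of about 0.33. The three proportions that readers would set side by side are each known only to about ±17 points.

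**3. Power of the dosimetry test, one cohort against a cohort-stratified test**

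Assumptions, not in the document: about half of patients deteriorate (in line with the plan's 50%), dose metric roughly normal, standardised dose difference d = 0.6 between those with and without deterioration, the same in every cohort, two-sided 5%. The Wilcoxon test has efficiency 3/π = 0.955 relative to the t test.

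Noncentrality: λ = d × √(0.955 × mn/(m+n)).

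- One cohort, 15 v 16: mn/(m+n) = 240/31 = 7.74; λ = 0.6 × √7.39 = 1.63. Power from the noncentral t with 29 df is 35%.
- Three cohorts, stratified: 3 × 7.74 = 23.2; λ = 0.6 × √22.2 = 2.83. Power is about 80%.
- The difference detectable with 80% power falls from 1.07 SD to 0.60 SD.

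Sensitivity to the split, by the normal approximation Φ(λ − 1.96), which gives 37% and 81% for the case above: if 30% deteriorate (9 v 22 per cohort), mn/(m+n) = 198/31 = 6.39, so λ = 0.6 × √(0.955 × 6.39) = 1.48 in one cohort and 1.48 × √3 = 2.57 across three. Power is about 32% and 73%. The gain persists.

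**The case against.** The strongest defence is that not comparing is the right decision. Modality is not randomised, SRT is closed to grade II, and the objectives are worded as reporting within each modality. The sentences about choosing a technique stand in the Abstract and Discussion, not among the objectives. This stands as a defence of the analysis: nothing here shows that the protocol ought to test modality against modality. It does not defend the claims. The statement about radiation type and dose per fraction comes from the section that sets out what the study will make it possible to evaluate.

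Cohort-by-cohort dosimetry tests also have a rationale, because 25 Gy in 5 Gy fractions and 50 to 60 GyRBE in 1.8 to 2 Gy fractions are not on one scale. This counts against simple pooling, but not against a test that ranks patients within cohort and then combines.

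Four stronger readings are tempting and are not supported:

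- That every analysis is confined to a cohort. The no-comparison statement is limited to patient-level objectives, the paired t test for quality of life names no cohort, and the planned NTCP and TCP models carry no per-cohort limit and may pool.
- That the within-cohort tests cannot bear on age or brain region. Eligible ages run from over 20 to under 65 within each cohort, and regional dose may be among the dosimetric data. An age model could be left to the full protocol or SAP.
- That the study is underpowered to compare cohorts. No such test is planned, so its power is not a defect.
- That an adjusted modality contrast in grade I patients is needed. It is a debatable trade-off: the number of grade I patients in IMRT and PRT is not given.

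**Conclusion.** The point holds as a mismatch between claims and plan. The effects of radiation type, of 5 Gy against 1.8 to 2 Gy fractions, and of modality are inseparable from cohort in this design, and the planned per-cohort proportions cannot guide a choice of technique. This follows from the current text and does not depend on an unseen SAP. The per-cohort primary estimate remains valid as a description.

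The second part is an avoidable loss of power in secondary analyses. Its size rests on the assumptions listed in the working, above all a broadly common association across cohorts and all 93 patients being assessable at 10 years. The within-cohort tests remain meaningful; they are weak on their own.

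**What to change.** 1. **Claims.** Restate the sentences in the Abstract (Methods), Hypothesis and expected clinical outcomes, and Discussion so that the results describe each cohort. Add that differences between cohorts, including those in radiation type and dose per fraction, cannot be attributed to modality, because modality is chosen by the clinician and SRT is not used in grade II.

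2. **Secondary tests.** Keep the per-cohort dosimetry and MRI results as descriptive. Add one cohort-stratified test over all irradiated patients: van Elteren for dosimetric data and Cochran-Mantel-Haenszel for MRI changes. Report a check of heterogeneity across cohorts with each. Van Elteren ranks within cohort, so it needs no fractionation correction.

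The cost is some rewording and two further analyses of data already due to be collected. With final results expected between 2030 and 2035, there is time to specify them in advance. The claims become more modest. The combined tests assume a broadly common association, and the heterogeneity check will itself have limited power at 31 per cohort. Stratifying by cohort does not adjust for confounding inside a cohort: in IMRT and PRT the prescribed dose range differs by grade, so the result should be reported as an association.
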